### **7.2 Safety instructions specific to the trial**

Patients must immediately contact the investigator in the event of unexplained symptoms or effects that may occur during or after the trial.

Serious adverse reactions can be “expected” (i.e. the safety outcomes that have been pre-defined) or “unexpected” if they would not be expected among perioperative patients given standard therapies and not previously described with fish oil supplementation. Previously described serious adverse reactions that are part of the clinical course of patients should be recorded on the case report forms. All serious adverse reactions, both expected and unexpected, need to be reported immediately (i.e. within 24 hours of knowledge of the event) to the Project Office by completing the appropriate Case Report Form. The Project Office will report all serious adverse reactions within Canada to Health Canada’s Natural Health Products Directorate (NHPD). If the serious adverse reaction is fatal or life threatening, the Project Office will notify the NHPD no later than seven days after knowledge of the event. If the serious adverse reaction is neither fatal nor life threatening, the Project Office will notify the NHPD no later than 15 days after knowledge of the event.

### **Emergency Unblinding**

Legitimate situations such as an adverse drug reaction may require unblinding. We recommend that all unblinding decisions be made jointly with the Project Office. The principal investigator should approve the request for unblinding wherever possible. If the local study investigator believes emergency unblinding is essential for the patient's management then it can be undertaken either by following the instructions provided in the Manual of Operations.

### **7.3 Premature Withdrawal/Discontinuation Criteria**

There are no known serious adverse effects of taking fish oil supplements. The most common side effect is gastrointestinal (GI) intolerance. If a study participant experiences severe GI intolerance which is suspected to be due to the study supplements, the following steps will be taken: 1) dose reduction – patient will only take 1 pill per day (instead of 2) for 2 weeks to see if this improves symptoms; 2) if symptoms persist, supplements will be discontinued for 2 weeks; 3) if symptoms improve, patient will be started on the 1 pill per day regime to see if tolerated; 4) if patient tolerates this treatment, full dosing will resume; 5) if symptoms reappear, patient will be permanently discontinued from the supplement. Patients will remain blinded, unless absolutely necessary.

## **8 STATISTICAL CONSIDERATIONS**

### **8.1 Study outcomes**

The aim of this study for the **Surgical Arm** is to determine whether the “no touch” technique results in a lower proportion of study SVGs that are totally (100%) occluded on 1-year post-CABG angiography, compared to conventional SVG harvesting techniques, and death due to cardiovascular or unknown causes. The aim for this study for the **Pharmacological Arm** is to determine whether N-3 polyunsaturated fatty acid (fish oil) oral supplementation results in a lower proportion of patients with  $\geq 1$  graft (study SVG, non-study SVG or arterial graft) totally (100%) occluded at 1-year post-CABG angiography, compared to those who received placebo. These events will be adjudicated, as defined in the operations manual.

### **8.2 Analysis population**

The main analysis will be by an intention-to-treat approach (i.e., all randomized patients in the study will be included in the analysis). At least 1,550 patients will be equally allocated to the four treatment groups.

### **8.3 Statistical Methods**

The primary comparison for the 2 main study questions (“no touch” vs. conventional SVG harvesting [primary endpoint: study SVG occlusion]; fish oil supplementation vs. placebo [primary endpoint: proportion of patients with >1 graft occluded]) will be performed using a Chi-square test according to the intention-to-treat principle. A test for interaction will be tested similarly and with logistic regression. Statistical significance is assumed for  $p < 0.05$ . The secondary graft occlusion endpoints, graft stenosis, or graft occlusion or significant stenosis, will also be tested with Chi-square or Fisher’s tests where appropriate, considering graft stenosis as a dichotomous variable, as well as logistic regression treating graft stenosis as an ordinal variable. Additional modeling will be performed post hoc with logistic regression, generalized estimating equation and bootstrapping techniques, to evaluate covariates of graft occlusion (7,18,71). Variables of interest in addition to the usual demographic factors include: open vs. endoscopic vein harvesting, serum lipid values; study centre; surgeon; time period of patient entry (to address a possible learning effect); timing of postoperative angiography; parameters related to the distal coronary artery target such as, size, quality, and factors related to the specific coronary artery grafted including the severity of the proximal stenosis. Other categorical outcomes (major cardiac events and vein harvest site complications) will also be compared with either Chi-square or Fisher’s Exact test where appropriate. The harvest site infection scores will be tested using t tests.

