## **5.5 Study measurements**

### **Study Outcomes**

#### **Primary Outcome**

***Surgical Intervention:*** The ***proportion of study SVGs*** (“no touch” versus conventionally harvested) which are totally (100%) occluded on 64-slice cardiac CT angiography at 1-year post-CABG and death due to cardiovascular or unknown causes.

***Pharmacological Intervention:*** The ***proportion of patients*** with  $\geq 1$  graft totally (100%) occluded on 64-slice cardiac CT angiography at 1-year post-CABG and death due to cardiovascular or unknown causes, comparing the fish-oil to placebo groups. Fish oils can theoretically affect patency of any of the bypass grafts (study or non-study, saphenous veins or arterial), although the effect would presumably be greatest in saphenous veins. We have therefore defined the primary outcome

for the pharmacologic intervention as the proportion of patients with at least 1 graft occluded (saphenous or arterial).

Any clinically directed angiogram (CTA or conventional) occurring up to 15 months postoperatively will contribute to the primary endpoint. Patients with poorly controlled atrial fibrillation or claustrophobia will be approached for conventional angiography. We anticipate from past experience that this will apply to <2% of patients.

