## 8.5 Sample size calculation

### A. SURGICAL ARM

The sample size estimation is based on the current prevalence of 1-year SVG occlusion using the conventional harvesting technique to be 20% (5,6). We consider a 30% relative risk reduction (RRR) in graft occlusion using the “no touch” technique to be a clinically important difference, consistent with RRRs reported for previous interventions to improve graft patency (antiplatelet therapy, use of statins post CABG, radial versus saphenous veins) and very conservative in terms of Souza’s clinical trial results (45,46). A sample size of 615 patients in each group will provide 80% power for a 2-tailed alpha of 0.05, to identify a RRR of 30% (20% occlusion rate in the control/ conventional harvesting group, to 14% in the experimental/”no touch” group – see Table 2a).

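### The primary test in Section 8.3 and the sizing in Section 8.5 (and Section 8.1 for fish oil) omit the cardiovascular or unknown-cause death that the defined primary outcomes include

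*Protocol*

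**What the plan says.** All references are to the protocol.

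- **Synopsis, Section 2 and Section 5.5.** Both primary outcomes combine total occlusion with death. Section 5.5 counts study vein grafts "totally (100%) occluded on 64-slice cardiac CT angiography at 1-year post-CABG and death due to cardiovascular or unknown causes" for the surgical comparison, and patients with one or more "graft totally (100%) occluded on 64-slice cardiac CT angiography at 1-year post-CABG and death due to cardiovascular or unknown causes" for fish oil. The two components are joined by 'and'. A later sentence of Section 5.5, explaining why any graft counts, restates the fish-oil outcome as "the proportion of patients with at least 1 graft occluded (saphenous or arterial") and leaves death out.
- **Section 8.1.** Death is kept for the surgical arm. The fish-oil aim ends at grafts "totally (100%) occluded at 1-year post-CABG angiography, compared to those who received placebo", without death.
- **Section 8.3.** The sentence defining the primary chi-square tests gives "primary endpoint: study SVG occlusion]; fish oil supplementation vs. placebo [primary endpoint: proportion of patients with >1 graft occluded". Death is in neither arm.
- **Section 8.5 and Tables 2a and 2b.** Both arms are sized on graft occlusion. The surgical calculation starts from a "20% occlusion rate in the control/ conventional harvesting group", and the fish-oil calculation from 30% of control patients with one or more grafts occluded.

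**The concern.** The section that defines the outcomes and the section that tests them name different primary endpoints. This is not detail left to an SAP. The protocol states the endpoint explicitly in each place, so an SAP that follows one section contradicts another.

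The difference changes who is analysed. Under Section 5.5, a patient who dies of a cardiovascular or unknown cause before the 1-year scan has had a primary event. Under Section 8.3 that patient has no angiogram and hence no outcome, although Section 8.2 promises that all randomised patients are included. Section 5.5 classes every death in the first 30 days as cardiovascular, so deaths that may follow early graft failure are among those dropped. Section 8.5 itself lists death among the reasons for missing angiography in the earlier trial it draws on.

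It also means that the stated power has not been worked out for the endpoint the protocol calls primary.

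**Working it through.** **Passages side by side**

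| Place | Death, surgical | Death, fish oil | Fish-oil graft count |
|---|---|---|---|
| Synopsis, Section 2, Section 5.5 | included | included | ≥1 |
| Section 8.1 | included | omitted | ≥1 |
| Section 8.3 | omitted | omitted | >1 |
| Section 8.5 | omitted | omitted | ≥1 |

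**Reproducing the plan's figures.** With two-sided alpha 0.05, 80% power, pooled variance and no continuity correction,

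n = [1.960·√(2p̄(1−p̄)) + 0.8416·√(p₁(1−p₁)+p₂(1−p₂))]² / (p₁−p₂)².

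- Surgical, 20% v 14%, p̄ = 0.17: (1.960 × 0.5312 + 0.8416 × 0.5295)² / 0.0036 = 614.1, so 615 as stated.
- Fish oil, 30% v 22.5%, p̄ = 0.2625: (1.960 × 0.6223 + 0.8416 × 0.6200)² / 0.005625 = 539.1, so 540 as stated.
- Power at 615 per group: 80.1% (surgical) and 84.9% (fish oil), matching the stated 80% and about 85%.
- Allowance for 20% without a scan: 615 / 0.80 = 768.75, so 769 as stated.

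The arithmetic is right, and it reproduces from occlusion rates alone, so no deaths entered the sizing.

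**Power for the composite.** Let d be the control-group proportion dying of cardiovascular or unknown cause by 1 year. The protocol gives no such figure. Its nearest number is an operative risk of death below 2%, in the section on risks to participants. I take d = 1–3% as an assumption and apply the occlusion rates to survivors:

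composite rate = d + (1 − d) × occlusion rate.

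The protocol does not state the effect of treatment on death, so three cases are shown at 615 evaluable per group.

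- (a) Same d in both groups.
- (b) Treated-group death is 0.8d.
- (c) The full relative reduction (30% surgical, 25% fish oil) applies to the composite.

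Cells give the treated-group rate and the power.

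| Arm | d | Control | (a) no effect | (b) 20% lower | (c) full reduction |
|---|---|---|---|---|---|
| Surgical | 1% | 20.8% | 14.9%: 78% | 14.7%: 80% | 14.6%: 82% |
| Surgical | 2% | 21.6% | 15.7%: 75% | 15.4%: 80% | 15.1%: 84% |
| Surgical | 3% | 22.4% | 16.6%: 73% | 16.1%: 81% | 15.7%: 85% |
| Fish oil | 1% | 30.7% | 23.3%: 84% | 23.1%: 85% | 23.0%: 86% |
| Fish oil | 2% | 31.4% | 24.1%: 82% | 23.7%: 85% | 23.6%: 87% |
| Fish oil | 3% | 32.1% | 24.8%: 81% | 24.4%: 86% | 24.1%: 88% |

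In case (a), 80% power needs 651 to 727 evaluable per surgical group against the planned 615. Fish oil needs 560 to 603, which 615 covers.

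Under the composite, patients who die are evaluable without a scan. Adding them to the 615 scanned (1–3% of 769, about 8 to 23 per group) leaves the case (a) ranges at 78–73% and 84–81%.

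**The case against.** **Section 5.5 governs.** It is the outcome-definition section, the synopsis and Section 2 agree with it, and Section 9.3 provides blinded adjudication of primary events to standard definitions. A reasonable statistician would probably follow it, and an unseen SAP may have settled the matter before unblinding. That makes a wrong analysis less likely. It does not remove the conflict: Section 8.3 is where the primary test is specified, and it labels a different quantity as the primary endpoint.

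**'And' merely lists components.** This is fair. A patient who died before 1 year cannot have a 1-year scan, so requiring both events would be nearly empty and 'or' is clearly meant. It should still be written.

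**'More than one graft' is a slip.** Almost certainly. Sections 2, 5.5, 8.1 and 8.5 all count one or more, and Section 5.5 also says so in words. A reader might infer that the trial is badly underpowered for an endpoint of two or more occluded grafts. The documents do not support that. Section 8.5 sizes one or more grafts, no control rate for two or more is given, and any power figure would rest on an invented model for an analysis nobody appears to intend.

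**Power need not fall.** This also stands. Adding deaths lowers power only if treatment leaves them unchanged. The meta-analysis cited in Section 1 reports an odds ratio of 0.80 for cardiac death with fish oil, which is close to case (b), where power is about as stated. For the harvesting technique the protocol gives no corresponding figure.

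**Early angiograms.** Section 5.5 says "Any clinically directed angiogram (CTA or conventional) occurring up to 15 months postoperatively will contribute to the primary endpoint". A reader might infer that an early scan showing patent grafts would settle 1-year status. The text says only that such scans contribute, and Section 5.2 schedules the study scan in a 9–15 month window. How scans before month 9 are handled is detail for the SAP or adjudication charter.

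**Conclusion.** The point holds for Section 8.3 (both arms), Section 8.5 (both arms) and Section 8.1 (fish oil only). It would be wrong to say that all of Section 8 departs from Section 5.5, because Section 8.1 keeps death for the surgical arm. The words "primary endpoint: study SVG occlusion" and their fish-oil counterpart describe an endpoint that drops deaths before the scan, which the defined primary outcomes count as events.

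The stated power is correct for occlusion only. A reader might conclude that it is too high, but that holds only if treatment has no effect on these deaths. Across assumed death rates of 1–3%, composite power runs from 73% to 85% (surgical) and from 81% to 88% (fish oil), depending on that unstated effect. The least favourable case costs about 7 points in the surgical arm (80% to 73%) and 4 in the fish-oil arm (85% to 81%). These ranges assume 615 evaluable patients per group and the protocol's occlusion rates among survivors.

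**What to change.** Use one definition per arm in the synopsis and Sections 2, 5.5, 8.1, 8.3 and 8.5:

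- Surgical: study vein graft totally occluded, **or** death from cardiovascular or unknown cause.
- Fish oil: one or more grafts totally occluded, **or** such a death.

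In Section 8.3, change '>1' to '≥1' and add the death component to both bracketed endpoints. Add it also to the fish-oil aim in Section 8.1 and to the explanatory sentence in Section 5.5. In Section 8.5, restate the control rate and power of each arm for the composite, giving the assumed death rate and the assumed effect of treatment on death.

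The cost is a wording amendment and a short recalculation, with no new data collection. If no effect on death is assumed, the sponsor must either accept stated surgical power a few points below 80% or raise the evaluable number from 615 to between 651 and 727 per group.

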| Demographics                           | ✓              |               |                  |               |              |              |              |               |
| Blood Work (creatinine)                | ✓              |               | ✓ a   |               |              |              |              | ✓             |
| Blood Work (CK-MB)                     | ✓              |               | ✓ b   |               |              |              |              |               |
| Medical History                        | ✓              |               |                  |               |              |              |              |               |
| Start Fish Oil Supplementation/Placebo | ✓ c |               |                  |               |              |              |              |               |
| Details of Surgical Procedure          |                | ✓             |                  |               |              |              |              |               |
| Patient Evaluation                     | ✓              |               | ✓                | ✓             | ✓            | ✓            | ✓            | ✓             |
| Clinical Outcomes                      |                |               | ✓                | ✓             | ✓            | ✓            | ✓            | ✓             |
| Leg Wound Assessment                   |                |               |                  | ✓             | ✓            |              |              | ✓             |
| Refills Given of Supplement/Placebo    |                |               | ✓                |               | ✓            | ✓            | ✓            |               |
| Supplement Compliance Checks           |                |               |                  | ✓             | ✓            | ✓            | ✓            | ✓             |
| ECG                                    | ✓              |               | ✓ d   |               |              |              |              | ✓             |
| Quality of Life Questionnaire          | ✓              |               |                  | ✓             |              |              |              | ✓             |
| Cardiac CT Angiography                 |                |               |                  |               |              |              |              | ✓             |

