### 5.4 Encouraging compliance

Noncompliance is not expected to be a major issue in this trial. The interventions are simple and the surgical intervention occurs at a single time-point and is controlled by the treating physician,

outcomes are objective, and data-forms are concise. Patient compliance to the study supplements will be monitored at follow-up visits via pill counts.

Patients are generally followed by their surgeons/cardiologists for several years after their procedure, and it is expected 99.9% follow-up at one month and over 99% follow-up at 6 months will be obtained. PHRI has substantial experience in documenting vital status in >99.5% in its clinical trials involving over 200,000 subjects recruited from over 50 countries and followed for up to 8 years. This expectation will be met in this study, especially with a post-surgical population in whom clinical follow-up by the surgeon for a minimum of 3 months is generally routine.

The overall study has been designed such that only one SVG is required to facilitate recruitment. We did consider restricting the study to patients who required at least 2 SVGs, as the event rates would presumably be greater. The chosen protocol does allow patients who are having only 2 grafts constructed (ITA and 1 SVG) and is compatible with patients undergoing more extensive arterial revascularization. We anticipate that the average number of vein grafts/patient will be 1.5 (as in GRIIP) (6). We considered restricting the control group to open harvesting rather than allow for endoscopic harvesting to be performed as well. We thought it important to include endoscopic harvesting as it is a commonly used technique, and there is recent evidence that endoscopic vein harvesting purports worse patency and clinical outcomes than conventional SVG harvesting (50). Although endoscopic patients will usually be unblinded, endpoint adjudication is blinded. Our post-hoc analysis will also aim to elucidate any difference in graft patency in the control SVGs harvested in the conventional open versus endoscopic techniques. We expect that the RRR will be similar or greater comparing endoscopic and no-touch versus open control and no-touch.

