### B. PHARMACOLOGICAL ARM

The literature suggests that fish-oils provide a RRR of about 25% compared to placebo (54,55, 65,69). Given a two-tailed alpha of 0.05, and an estimated 30% of control patients with  $\geq 1$  graft occluded at 1-year, a sample of 540 patients in each group (fish-oil versus placebo) will provide a power of 80% to detect a RRR of 25%. A sample size of 615 patients (required for the surgical intervention) provides approximately 85% power to test the fish oil hypothesis (see Table 2b).

We anticipate that 80% of patients will undergo 1-year coronary CT angiography, which is consistent with our past trial experience (7). The primary reason that patients failed to undergo late angiography in RAPS was late withdrawal of consent in 77 patients, protocol violation in 17 patients, new contraindication precluding research angiography in 19 patients and death in 8 patients (7). To adjust for this potential loss to follow-up angiography, the corrected sample size is 769 patients in each surgical group to ensure adequate statistical power when making our conclusions for both arms of the factorial design. Thus we aim to recruit a **total of 1,550** patients for the overall study across ~50 participating sites, 10 Canadian and the remaining International. The pilot phase will recruit 50 patients from 10 sites (5 Canadian and 5 International). Pilot patients will be included in the final analysis. *While MACE between groups will be tested using the total sample size, we will only be able to detect very large differences at 1 year, as MACE is expected to be approximately 10 - 12% (6,7,17).*

**Table 2a:** Sample Size Estimates for Primary Endpoint (Surgical Arm) – 1-Year Graft Occlusion (two-tailed  $\alpha=0.05$ ,  $\beta=0.20$ )

| Control Event Rate | Relative Risk Reduction |             |                     |             |                     |             |                     |             |                     |             |
|--------------------|-------------------------|-------------|---------------------|-------------|---------------------|-------------|---------------------|-------------|---------------------|-------------|
|                    | 20%                     |             | 25%                 |             | 30%                 |             | 35%                 |             | 40%                 |             |

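### Fish-oil primary analysis: the unadjusted chi-square is valid but gives up a little precision, because risk rises with the number of grafts and randomisation is stratified

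*Protocol*

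**What the plan says.** Section 8.3 of the Protocol fixes the test: "fish oil supplementation vs. placebo [primary endpoint: proportion of patients with >1 graft occluded]) will be performed using a Chi-square test". Logistic regression appears there for the interaction test, for ordinal stenosis and for covariates of graft occlusion. The covariate work is labelled post hoc, and the variables it names do not include the number of grafts.

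Section 5.5 defines the fish-oil endpoint as the "proportion of patients with at least 1 graft occluded (saphenous or arterial"), together with death from a cardiovascular or unknown cause. Its reason for counting every graft is that "Fish oils can theoretically affect patency of any of the bypass grafts (study or non-study, saphenous veins or arterial"). The >1 printed in 8.3 disagrees with the at-least-one definition in the synopsis and in sections 2, 5.5 and 8.1. That discrepancy is a separate matter; at least one is used below.

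Graft number varies by design. Section 5.4 admits patients with one internal thoracic artery graft and one vein graft, and states: "We anticipate that the average number of vein grafts/patient will be 1.5". It also says that restricting entry to patients with two or more vein grafts was considered, since event rates would presumably be higher.

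Section 3.3 stratifies randomisation by site and, following the pilot, by open or endoscopic control technique. Section 3.1 blinds patients and all care providers to the supplement.

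**The concern.** An indicator of any occluded graft depends on how many grafts the patient has, whatever the supplement does. Graft number is therefore a prognostic factor built into this endpoint, and section 5.4 shows that the authors recognised it. A test that ignores it leaves explainable between-patient variation in the error term. The same holds for site and control technique, which are used to stratify randomisation but not in the analysis. What is at stake is a modest amount of power and precision in one of the two primary comparisons. Adjustment also has to be fixed in advance to be credible as primary, and 8.3 offers only a post hoc route.

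**Working it through.** **1. The plan's own figures.** Inputs from section 8.5: 30% v 22.5% (relative reduction 25%), two-sided alpha 0.05.

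- Size: n = [1.96·√(2·0.2625·0.7375) + 0.8416·√(0.30·0.70 + 0.225·0.775)]² / 0.075² gives 540 per group, as stated.
- Power at 615 per group: the null SE is √(2·0.2625·0.7375/615) = 0.0251 and the alternative SE is √((0.21 + 0.1744)/615) = 0.0250. Then (0.075 − 1.96·0.0251)/0.0250 ≈ 1.03, so power is 84.9%. The Protocol says approximately 85%.

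**2. The mechanism.** With k vein grafts, per-vein occlusion q and arterial occlusion a, and grafts independent, P(at least one occluded) = 1 − (1 − a)(1 − q)^k. Section 8.5 gives q = 20% for conventional harvest. With a = 0, risk is 20% for one vein graft and 36% for two. With a = 5% (assumed) it is 24% and 39%. A 50/50 mix averages 28 to 32%, consistent with the planned 30%.

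**3. The gain.** The Protocol gives only the mean of 1.5 vein grafts, so the mixes below are assumptions with that mean. In each, q is set so that overall control risk is 30%, and the relative reduction is 25% at every graft number. R² = Var(P)/[mean·(1 − mean)], using risks averaged over the two groups.

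- Column A: occlusion only, independent grafts, a from 5% down to 0; power from the variance stratified by vein-graft number.
- Column B: as A with a = 0, plus an assumed 2% death component; power at an effective n of 615/(1 − R²).
- Column C: as A with a = 5%, plus an assumed latent within-patient correlation of 0.4; power as in B.

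| Mix of vein-graft numbers | A: R², power | B: R², power | C: R², power |
|---|---|---|---|
| 50/50 with 1/2 | 2.1–2.8%, 85.7–85.9% | 2.5%, 85.8% | 1.4%, 85.4% |
| 60/30/10 with 1/2/3 | 3.3–4.5%, 86.1–86.5% | 4.0%, 86.3% | 2.1%, 85.7% |
| 70/15/10/5 with 1/2/3/4 | 5.0–6.5%, 86.7–87.2% | 5.9%, 87.0% | 3.0%, 86.0% |

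Column A is the favourable case, because it omits death and correlation. With these allowed for, R² is about 1.4 to 6%. Effective size is then 615/0.986 ≈ 624 to 615/0.94 ≈ 654 per group, and power about 85.4 to 87.0%. Applying death and correlation together lowers the smallest R² to about 1.3%, with power still about 85.4%.

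**4. Simulation under column A** (100,000 trials per scenario): the chi-square has power of about 0.85 and a Mantel-Haenszel test stratified by vein-graft number 0.856 to 0.871. Type I error is about 0.05 for both.

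**5. Chance imbalance.** In the 60/30/10 mix the SD of vein-graft number is √0.45 = 0.67, so the SE of the group difference in mean is 0.67·√(2/615) = 0.038. At about 0.15 extra risk per vein graft, a one-SE imbalance moves the risk difference by about 0.6 points. The SE of the risk difference is 2.5 points and already contains this.

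The contribution of site and control technique cannot be computed, because the Protocol gives no between-site variation.

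**The case against.** The case for leaving 8.3 alone is respectable. The chi-square is simple, needs no model and matches the sample-size calculation. Randomisation balances graft number in expectation, and the comparison already has about 85% power against a target of 80%. Covariate choice is often settled in a statistical analysis plan, which is not shown here. All of this stands as to validity and size. It does not remove the point, because 8.3 itself names an unadjusted primary test and makes the modelling post hoc.

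Three practical objections also stand, and they shape the fix:

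- No sentence says that graft number is recorded. A reader may infer it from the Table 1 row "Details of Surgical Procedure" and from the secondary outcome that treats venous and arterial grafts separately. Scoring the endpoint also requires knowing each scanned patient's grafts. It remains an inference, and a planned graft number is nowhere said to be captured: section 5.1 has the surgeon identify only the study graft's proposed target beforehand.
- The actual number is fixed at surgery, after randomisation and after supplements begin. It does not exist for anyone randomised but not operated on, whereas section 8.2 analyses all randomised patients.
- About 1,230 scanned patients over some 50 sites is roughly 25 per site, so separate site terms would be sparse.

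A reader might go further and infer that the chi-square is biased or invalid, or that chance imbalance in graft number is an additional hazard. The documents support neither: type I error is unaffected, and the imbalance is already in the standard error. Nor is the crude test without merit, given its simplicity.

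**Conclusion.** The point holds as a small efficiency improvement. Section 8.3 fixes a valid unadjusted test for an endpoint whose risk rises with graft number, and ignores the randomisation strata. For graft number alone the gain is about 0.5 to 2 percentage points of power at 615 per group, from 84.9% to about 85.4 to 87%, with R² of about 1.4 to 6%. This rests on assumed graft mixes with mean 1.5, arterial occlusion of 0 to 5%, correlation of 0 to 0.4, and a constant relative reduction. The trial is adequately powered for this comparison on its own assumptions without the change. The argument does not carry over to the surgical primary endpoint, which has one study graft per patient and an unblinded surgeon.

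**What to change.** In section 8.3, pre-specify the fish-oil primary analysis as a logistic model, or a stratified Mantel-Haenszel analysis, with:

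- supplement;
- randomised harvest technique, the other factor of the 2x2 design, which acts on the same grafts;
- number of vein grafts;
- the randomisation strata, with small sites pooled or site as a random effect.

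Report the marginal (standardised) risk difference and relative risk, so that the target stays that of the planned comparison of proportions. Keep the chi-square as a supporting analysis.

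Preferably use the number of vein grafts planned before randomisation, captured as one CRF field. If the actual number is used, justify it by the blinding of supplement allocation, and state a rule for randomised patients not operated on, for example the planned number or a missing category. Do not apply the graft-number adjustment to the surgical primary endpoint.

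The cost is a sentence or two in 8.3, one CRF field and a slightly more complex primary analysis. No extra patients or visits are needed.
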